#### 2.6.2 Secondary Outcomes

1. Changes in visual analogue scale (VAS): Measurement will be performed at every visit.2. Changes in patient’s global assessment of disease activity (PGA) and physician’s global assessment of disease activity (MDGA): Measurement will be performed at every visit.3. Changes in clinical disease activity index (CDAI) and simplified disease activity index (SDAI): Measurement will be performed at every visit. The evaluation methods were described carefully in a former study (Aletaha and Smolen, 2005).4. Changes in disease activity score 28 (DAS28): Measurement will be performed at every visit. The evaluation methods were described carefully in a former study (Prevoo et al., 1995).5. Changes in TCM syndromes efficacy score scale: TCM syndromes efficacy score ranges from from 0 to 45. Measurement will be performed at every visit.6. Changes in Health Assessment Questionnaire-Disability Index (HAQ-DI): Measurement will be performed at baseline and week 48. The evaluation methods are available at Khanna et al. (2005).7. Changes in FACIT-Fatigue score scale: Measurement will be performed at baseline and week 48. The evaluation methods are available in the Yellen et al. (1997) study.8. Changes in color Doppler ultrasound semi-quantitative score of joints. Measurement will be performed at baseline and week 48. We consider an ultrasound score based on 7 joints of the clinically dominant hand and foot evaluation methods (Backhaus et al., 2009).9. Changes in CRP, ESR, RF, and anti-CCP. CRP and ESR will be performed at every visit. RF and anti-CCP will be performed at baseline and week 48.

#### 2.6.3 Safety Outcomes

AEs will be monitored for 48  weeks from the time when the subject signed the informed consent and enrolled in the trial to the last follow-up. Especially, visit 2 (4 weeks ± 2 days) is set to monitor the AEs. The description of severity (grades) and system organ class (SOC) of AEs will follow the Common Terminology Criteria for Adverse Events (CTCAE) Version 5.0 (SERVICES, 2017). The AEs would be coded using the current version of the Medical Dictionary for Regulatory Activities (MedDRA). The relationship between AEs and intervention will be judged according to the adverse drug reaction report and testing manual published by the Department of Drug Safety Supervision, State Food and Drug Administration of the People’s Republic of China (Guan et al., 2008).

### 2.7 Participant Timeline

The study will last 3 years: from July 2019 to July 2022. The timeline and study procedure are available in Table 3 and Figure 1.

**TABLE 3 T3:** Study procedure table.

Visit Project	Screen period (baseline)		Visit			
	1		2	3	4	5
Time of visit	−4 weeks-0 days	0 ± 2 days	4 weeks ± 2 days	12 weeks ± 3 days	24 weeks ± 5 days	48 weeks ± 5 days
General information	●					
Family history	●					
Medical history	●					
Drug allergy history	●					
Pre-trial medication*	●					
Vital signs	●		●	●	●	●
Physical examination	●			●	●	●
Laboratory examination						
Routine blood test	●		●	●	●	●
CRP	●			●	●	●
ESR	●			●	●	●
Routine urine/stool test	●			●	●	●
RF + ASO	●			●	●	●
Blood biochemical examination**	●		●	●	●	●
ACPA	●					●
Color Doppler ultrasound		●		●	●	●
Other laboratory results		●		●	●	●
Pre-RA diagnosis	●					
Evaluate RA conversion			●	●	●	●
TCM syndrome diagnosis	●					
Inclusion/exclusion criteria	●					
Screening results	●					
Sign informed consent form	●					
Evaluate disease activity (DAS28/PGA/CDAI/SDAI/VAS)		●		●	●	●
TCM symptom integral		●		●	●	●
Health Assessment Questionnaire-Disability Index		●				●
FACIT-Fatigue Scale		●				●
Suspension standards			●	●	●	●
Prescription		●	●	●	●	●
Combined drugs***		●	●			
Adverse event***		●	●	●	●	●
Distribution of medicine by express mail		●	●	●	●	●
End of study summary						●

*Record medications that were used and discontinued prior to the study. Drugs that were not discontinued prior to the study and entered the treatment period should be recorded in “Combined Drugs”. **Only liver function needs to be tested at 2 weeks. ***Observe continuously throughout the study and record when it occurs.

**FIGURE 1 F1:**
[figure not shown]
The flow diagram of the study.

### 2.8 Sample Size

Based on the primary outcome, we use the model of “tests for two proportions” in PASS 15.0. Alternative hypothesis: two-sided. Test type: Z-test (unpooled). Power was set at 0.9 and alpha was set at 0.05. The intervention group and control group were allocated a 1:1 ratio. The effect size of the treatment group (P1): based on the results of our former small sample of observational study (results unpublished), about 53.26% of patients would transit to RA after 1 year of TCM treatment. The effect size of the control group (P2): without any medication interventions, about 70% of early-stage UA patients with ACPAs meet the 1987 ACR criteria 1-year follow-up (Firestein et al., 2016). We would need 173 subjects in each group. Predicting a 10% dropout rate, the subjects rise to 385. Considering there were 13 centers that took part in the studies, the final subject was set at 390 (30 subjects per center).

### 2.9 Recruitment

For achieving adequate participant enrolment: 1) We placed the recruitment advertisement in the hospital outpatient waiting hall; 2) we published the announcement in a WeChat individual official account (one of the most popular social networking software in China); and 3) we referred patients who meet inclusion criteria in cooperation with primary care units.

### 2.10 Allocation, Sequence Generation, Blinding, and Implementation

Drug clinical trial data management system [abbreviated as electronic case report form (eCRF) system)] developed by Nanjing Haitai Medical Information System Co., Ltd. is a secure web application for building and managing online surveys and databases. Sequence generation: a multicenter block random method was used. The random number of multicenter groups was generated through the corresponding randomization program of SAS software (version 9.4). The relevant parameters and results of the SAS randomization program were saved by Zhejiang Chinese Medical University (study design unit). The sequence was uploaded to the eCRF system and researchers took part in the study retrieve sequence for recruiting patients. [name] (one of the designers), outcome assessors, and workers in the drug manufacturing center are not masking (participants and investigators are blinding). In the real practice of TCM diagnosis and treatment, TCM doctors usually prescribe 14-d to 28-d treatment based on the patients’ symptoms and TCM patents. Thus, the researchers would upload the prescriptions and patient express information to [name] for simulating a real TCM situation. Subsequently, [name] would upload patient express information and which drug (placebo or YQCF, including drug compatibility) the manufacture center will process. The product would be delivered to the patients directly based on their express information. All the participants who save the patient personal privacy information strictly abide by the confidentiality regulations.

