## Abstract

**Introduction:** Rheumatoid arthritis (RA) is an autoimmune disease characterized by progressive bone erosion on diarthrodial joints. RA patients usually experienced three stages before final diagnosis: the health period, the pre-clinical period (immune response exists without clinical symptoms), and the pre-RA period (immune response exists with mild inflammatory manifestation). Presently, there is seldom guidance referring to early intervention which is a benefit for stable disease conditions and low morbidity. Prophylactic treatment is a major feature of traditional Chinese medicine (TCM). In this present study, a multi-center, double-blind, placebo-controlled clinical trial is carried out to evaluate both efficacy and safety in preventing RA progression on Yunpi Qufeng Chushi formula (YQCF).

**Method:** The multi-center, double-blind, placebo-controlled clinical trial is conducted in 13 hospitals nationwide. A total of 390 patients ages between 18 and 70 will be recruited in the trial. They will be randomly assigned to the intervention group (YQCF) and placebo group. The follow-up visit will be taken every 3 months from baseline to 1 year. Diagnosis, disease activity scores, clinical disease activity index (CDAI), simplified disease activity index (SDAI), TCM syndrome scores, and safety assessments will be recorded at every visit. Joint color doppler ultrasound, health assessment questionnaire-disability index (HAQ-DI), and functional assessment of chronic illness therapy-fatigue (FACIT-F) will be recorded at baseline and the last visit.

**Discussion:** This work will provide evidence of YQCF in preventing RA progression. However, whether early intervention would benefit the controlling RA disease still needs a long-term follow-up.

**Ethics and dissemination:** Protocol version 2 (201910-1). This research was approved by the medical ethics committee of Zhejiang Chinese Medical University (2019-045). Results will be published in a peer-reviewed academic journal.

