## 2 Materials and Methods

### 2.1 Study Setting

The multi-center, double-blind, placebo-controlled clinical trial is conducted in 13 hospitals nationwide including First Affiliated Hospital of Zhejiang Chinese Medical University, Second Affiliated Hospital of Zhejiang Chinese Medical University, Third Affiliated Hospital of Zhejiang Chinese Medical University, Xiyuan Hospital of China Academy of Chinese Medical Sciences, Guanganmen Hospital of China Academy of Chinese Medical Sciences, Dongfang Hospital of Beijing University of Chinese Medicine, China-Japan Friendship Hospital, Shanghai Hospital of Traditional Chinese Medicine, First Affiliated Hospital of Zhejiang University School of Medicine, Second Affiliated Hospital of Zhejiang University School of Medicine, Sir Run Shaw Hospital of Zhejiang University School of Medicine, First Affiliated Hospital of Guangzhou University of Traditional Chinese Medicine, and First Affiliated Hospital of Anhui University of Chinese Medicine.

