### 2.2 Participants

A total of 390 participants aged 18–70 will be recruited. Inclusion and exclusion criteria are presented as follows.

To date, the definition (or criteria) of pre-RA is controversial. We propose our definition based on the trials mentioned above. For the patients with positive anti-CCP antibodies: at least 1 joint involvement (any swollen or tender joint on examination) and do not meet any RA classification criteria [ACR 1987 revised criteria (Arnett et al., 1988) and ACR/EULAR 2010 criteria (Aletaha et al., 2010)]. For the patients with negative anti-CCP antibodies: meet with at least 5 parameters according to the EULAR definition of arthralgia suspicious for progression to RA (van Steenbergen et al., 2017) (details available in Table 1).

**TABLE 1 T1:** EULAR defined characteristics describing arthralgia at risk for RA (adapted from van Steenbergen et al., 2017).

History taking
1. Joint symptoms of recent onset (duration <1 year)
2. Symptoms located in MCP joints
3. Duration of morning stiffness ≥60 min
4. Most severe symptoms present in the early morning
5. Presence of a first-degree relative with RA
Physical examination:
6. Difficulty with making a fist
7. Positive squeeze test of MCP joints

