### 2.6 Outcomes

#### 2.6.1 Primary Outcomes

##### 2.6.1.1 RA Transition Rate

Definition: pre-RA patients who fulfill any criteria of RA classification at any time will be defined as “RA transition.” Survival time will be recorded as the number of days between the date of informed consent and the date of transition.

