In this study, the following measures have been taken for diagnosis and differential diagnosis of pre-RA: according to the RA classification criteria, joint involvement, up to 5 scores and only 1 point away from the RA diagnostic threshold, is defined as: any swollen or tender joint on examination, which may be confirmed by imaging evidence of synovitis (Aletaha et al., 2010). The exact joint involvement assessment is critical in pre-RA diagnosis. Both ultrasound and MRI are effective techniques to evaluate joint inflammation. However, in view of the advantages of low cost and convenience, ultrasound may be a better choice in pre-RA diagnosis (Xu et al., 2017). Other anti-nuclear antibodies (ANA) also would be detected at baseline for diagnosing other rheumatoid diseases.

This study also has certain limitations. The sample size and trial duration are calculated based on the anti-CCP-positive individuals. Anti-CCP level not only affects the efficacy of DMARDs but also is related to the onset time of arthritis (Burgers et al., 2017). Anti-CCP-positive individuals are more likely to develop arthritis and RA as compared to anti-CCP-negative individuals. More subjects and longer follow-up visits are needed in prognosis analysis. The guidelines published by ACR and EULAR stated that an early treat-to-target (T2T) strategy will improve outcomes, such as bone erosions (Smolen et al., 2020; Fraenkel et al., 2021). However, due to the limited observation time, we cannot answer whether the use of TCM schemes can achieve better outcomes.

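### Section 2.10 states that outcome assessors are not masked and does not say who judges RA transition, so the primary endpoint may be open to detection bias

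*Protocol article*

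**What the plan says.** Section 2.10 of the protocol article names one designer as not masked and continues: "outcome assessors, and workers in the drug manufacturing center are not masking (participants and investigators are blinding". The same section describes supply: researchers send prescriptions to the designer, the designer tells the manufacturing center which product to make, and the product goes straight to the patient.

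The trial is described as double-blind throughout, for example in section 2.1: "The multi-center, double-blind, placebo-controlled clinical trial is conducted in 13 hospitals nationwide".

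The primary outcome in section 2.6.1.1 counts "pre-RA patients who fulfill any criteria of RA classification at any time will be defined as “RA transition". Table 3 schedules an evaluation of RA conversion at visits 2, 3, 4 and 5 but does not assign it to anyone. On the weight of the joint findings, the Discussion says: "joint involvement, up to 5 scores and only 1 point away from the RA diagnostic threshold, is defined as: any swollen or tender joint on". The sentence then refers to the clinical examination and allows imaging as possible confirmation. Section 2.6.2 lists DAS28, CDAI, SDAI and a semi-quantitative joint ultrasound score among the secondary outcomes.

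**The concern.** The designer and the manufacturing workers need the allocation to prepare and send the right product. Nothing in the supply chain requires an outcome assessor to know it. An assessor who does know it, and who also examines joints or decides whether the criteria are met, may call borderline findings differently in the two arms.

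The endpoint definition gives such differences room to act. Meeting either set of criteria at any visit counts, so one differential call at any of four visits creates an event, and nothing in the definition reverses it. Patients enter without meeting the criteria (stated in section 2.2 for the anti-CCP-positive group), so judgements made after randomisation determine the result. At stake is whether a difference in transition rates can be credited to the treatment.

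**Working it through.** **1. Who is masked, and who assesses.**

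| Role | Masking (2.10) | Stated need for allocation |
|---|---|---|
| One designer | Not masked | Yes, assigns the product |
| Manufacturing workers | Not masked | Yes, make and send it |
| Outcome assessors | Not masked | None given |
| Participants | Masked | – |
| Investigators | Masked | – |

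No section masks the assessors elsewhere or provides for blinded adjudication of transition. No section says whether investigators or separate assessors carry out the joint examination, the ultrasound scoring or the transition judgement.

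**2. Which outcomes could be affected.** Examiner-dependent: the joint component of the RA criteria, the joint counts in DAS28, CDAI and SDAI, and the ultrasound score. Not examiner-dependent: CRP, ESR, RF and anti-CCP (laboratory values), and VAS and the patient's global assessment (rated by the masked patient).

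**3. The plan's own sample size (section 2.8).** Inputs: P1 = 0.5326, P2 = 0.70, two-sided alpha 0.05, power 0.90, unpooled Z-test, 1:1 allocation.

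n per arm = (1.960 + 1.282)² × [P1(1 − P1) + P2(1 − P2)] / (P2 − P1)²
= 10.507 × (0.2489 + 0.2100) / 0.02802 = 172.08, rounded up to 173.

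With 10% dropout: 346 / 0.9 = 384.4, rounded up to 385, as stated. The calculation is sound on its inputs, and masking the assessors does not change it.

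**4. Illustration of the possible size.** Assumptions not in the document: no true effect, and a net difference d between arms in the proportion called transitioned, arising from assessment alone. The base rate of 62% is close to the mean of the two planning rates, (0.5326 + 0.70) / 2 = 0.616. Set a = 0.62 − d/2 and b = 0.62 + d/2, with n = 173:

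SE = √{[a(1 − a) + b(1 − b)] / n}; rejection rate = Φ(d/SE − 1.96) + Φ(−d/SE − 1.96)

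| d (points) | SE | d/SE | Rejection rate | Share of planned 16.74-point effect |
|---|---|---|---|---|
| 0 | – | 0 | 5% | 0% |
| 2 | 0.0522 | 0.383 | 6.7% | 12% |
| 5 | 0.0521 | 0.959 | 16.0% | 30% |
| 10 | 0.0519 | 1.926 | 48.7% | 60% |

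At 173 per arm, over base rates from 53.26% to 70%, the ranges are 6.6–6.9%, 15–17% and 47–53%. At 195 per arm (390 / 2) and 62%, the three rates are 6.9%, 17.5% and 53.4%. A larger sample makes a false positive from a fixed bias more likely.

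**5. Whether the analysis could correct it.** Section 2.12.1 plans chi-square or Fisher tests, Kaplan-Meier analysis and logistic regression, on ITT and per-protocol sets. All take the recorded transition as given, so none can remove a difference that arises when transition is recorded.

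**The case against.** The strongest reply is that the sentence calling assessors unmasked also says investigators are blinded. If those investigators examine the joints and judge transition, the route to bias largely closes and the sentence is a wording fault. The document does not settle this, so actual bias is conditional. What stands in either case is that the sentence must be corrected or explained.

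Several stronger readings are tempting but not supported:

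- *The double-blind label is false.* Section 2.10 names the two blinded parties as participants and investigators, and the label fits that usage. The weakness is the unmasked assessor.
- *Calling one extra joint makes a patient a case.* The Discussion says only that joint involvement can score up to 5, one point short of the threshold. The article gives no per-joint scoring, so one joint matters only for a patient already at a boundary.
- *The endpoint is simply a joint count.* The Discussion describes joint involvement as leaving a patient short of the threshold, so other components must contribute. The remarks "any swollen or tender joint on examination" in section 2.2 and "The exact joint involvement assessment is critical in pre-RA diagnosis" in the Discussion concern entry to the trial and bear on the endpoint only indirectly.
- *Adverse-event causality is judged unmasked.* Section 2.6.3 names a manual for this judgement but not the person who makes it.
- *A positive result would be uninterpretable.* That depends on the size of the bias, which is unknown; a 2-point difference barely moves the error rate.

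**Conclusion.** The point holds in conditional form. It is certain that section 2.10 places outcome assessors among the unmasked without a reason or safeguard, and that the article does not say who judges RA transition. It is conditional that the primary endpoint and the examiner-dependent secondary outcomes are biased: that requires unmasked staff to make those assessments and to call findings differently by arm. The error rates of about 7%, 16% and 49% show what net differences of 2, 5 and 10 points would do. They are not estimates for this trial. Because the primary conclusion is exposed if the text is followed as written, and no planned analysis would repair it, the passage needs to be changed.

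**What to change.** Rewrite section 2.10 to state who performs the joint examination, the ultrasound scoring and the RA-transition judgement, and require that these people are masked. The already blinded investigators could do this, with allocation hidden in their eCRF view. Leave only the drug-assignment role and the manufacturing workers unmasked. If the sentence is a wording error, correct it.

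If assessments have already been made unmasked:

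- flag them in the database;
- keep all randomised patients in the ITT primary analysis, since dropping those assessed unmasked would break the ITT set and could leave few or no patients;
- as a sensitivity analysis, re-derive transition from the recorded criteria components without sight of allocation;
- disclose the unmasked assessment wherever the trial is described as double-blind.

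The cost is a wording and access-rights amendment and a little extra analysis. No new staff are needed if the blinded investigators or assessors who can still be masked do the scoring; assessors who already know allocations may have to be replaced. Masking cannot be restored for assessments already made, and the re-derivation cannot undo bias in the recorded joint findings themselves.

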### 2.11 Data Collection Methods and Management

Data will be collected in the paper and electronic CRF via the clinic and the Internet (using the eCRF system), respectively. Paper CRF will be delivered to clinical centers. Training and support for using the eCRF system will be made available to researchers by the Zhejiang Chinese Medical University. For promoting participant retention and complete follow-up, first-line investigators will inform the patients when they should go to the hospital to complete follow-up via telephone and WeChat. Two independent investigators will check the data values.

### 2.12 Statistical Methods

#### 2.12.1 Primary Outcome

The final RA transition rate will be performed by Pearson’s chi-square or Fisher’s exact chi-square tests. In addition, RA transition survival analysis will be performed by Kaplan-Meier survival analysis. Binary logistic regression is utilized to investigate the multiple variables which can affect RA transition rate. The variables include sex, age, anti-ccp and RF state, family history, DAS28, continuous NSAIDs use, and YQCF use. Per-protocol (PP) analysis and intention-to-treat (ITT) analysis will be applied in chi-square tests, survival analysis, and binary logistic regression.

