
Nonsteroidal anti-inflammatory drugs (NSAIDs) will be allowed to be prescribed when the patients suffer from pain. DAMARs and glucocorticoids will not be allowed in the study. The untaken drug will be returned.

Mild and moderate adverse events (AEs) will change the composition of YQCF granules according to the relative granules AEs. For example, Sinomenium acutum (Thunb.) Rehder and E.H. Wilson will be removed because it would cause cutaneous pruritus. Severe AEs will stop the intervention and the patient will withdraw.

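### The supporting logistic model for RA transition adjusts the YQCF effect for what reads as on-trial NSAID use, so its odds ratio is not the total randomised effect

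*Protocol article*

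**What the plan says.** Section 2.12.1 (Primary Outcome) describes three analyses of RA transition. The first is an unadjusted comparison: "The final RA transition rate will be performed by Pearson’s chi-square or Fisher’s exact chi-square tests". The second is Kaplan-Meier. The third is a multivariable model: "Binary logistic regression is utilized to investigate the multiple variables which can affect RA transition rate". Its covariates are listed: "The variables include sex, age, anti-ccp and RF state, family history, DAS28, continuous NSAIDs use, and YQCF use". All three are to be run in two analysis sets: "Per-protocol (PP) analysis and intention-to-treat (ITT) analysis will be applied in chi-square tests, survival analysis, and binary logistic regression".

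The only rule on NSAIDs is in section 2.5 (Interventions): "Nonsteroidal anti-inflammatory drugs (NSAIDs) will be allowed to be prescribed when the patients suffer from pain". In Table 3 (section 2.7) the footnote attached to combined drugs reads: "Observe continuously throughout the study and record when it occurs". Pain is the first secondary outcome in section 2.6.2: "Changes in visual analogue scale (VAS): Measurement will be performed at every visit".

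The covariate list does not say whether NSAID use or DAS28 is taken at baseline.

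**The concern.** A covariate in a model that estimates a randomised treatment effect should be fixed before randomisation. NSAIDs prescribed for pain during the 48 weeks are not. If YQCF eases symptoms, fewer YQCF patients will need NSAIDs. NSAID use will also tend to mark patients whose disease is more active and who are nearer to RA.

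Conditioning on it then does two things. It removes whatever part of the YQCF effect runs through symptoms. It also compares YQCF patients who still need NSAIDs with placebo patients who need them, and these two groups are no longer alike in underlying severity.

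What is at stake is the YQCF odds ratio from this one model. It is the only covariate-adjusted analysis of the primary outcome that the article describes. It sits under the primary-outcome heading and is run in the ITT set, so it is likely to be reported as the adjusted treatment effect.

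**Working it through.** **1. The plan's own figures.** Section 2.8 gives transition rates of p1 = 53.26% (YQCF) and p2 = 70% (control), with an unpooled two-sided Z-test. It also states: "Power was set at 0.9 and alpha was set at 0.05".

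n = (z0.975 + z0.90)² × [p1(1−p1) + p2(1−p2)] / (p1−p2)² = 10.507 × 0.45894 / 0.028023 = 172.08, so 173 per group, as stated.

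With 10% dropout, 346/0.9 = 384.4, so 385, as stated. The sizing rests on an unadjusted comparison and does not involve the NSAID term.

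**2. The odds ratio implied by the design rates.** (0.5326/0.4674) / (0.70/0.30) = 1.1395/2.3333 = 0.488.

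**3. What adding the NSAID term does.** The document gives neither the rate of NSAID use, nor the effect of YQCF on it, nor its link with RA. The inputs in this step are therefore assumptions.

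- Severity U is standard normal and has the same distribution in both arms.
- NSAID use: logit P(NSAID) = a_T + sU, with a_T set to give the assumed rate in arm T.
- RA transition: logit P(RA) = b_T + sU, with b_T set to give 70% and 53.26%, or 70% in both arms for the null case.
- Given U and arm, NSAID use has no direct effect on RA.
- The slope s is 0.5, 1 or 1.5 per SD of severity.

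RA transition is then regressed on arm and NSAID use in the large-sample limit. Ranges are over the three slopes:

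| Assumed NSAID use, placebo vs YQCF | Design OR 0.488 becomes | Null OR 1.00 becomes |
|---|---|---|
| 50% vs 50% | 0.46-0.49 | 1.00 |
| 50% vs 40% | 0.50-0.52 | 1.02-1.13 |
| 50% vs 30% | 0.51-0.59 | 1.05-1.28 |
| 60% vs 30% | 0.52-0.68 | 1.07-1.46 |

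In the first row the small shift in the design OR is only the non-collapsibility of the odds ratio; the null stays at 1.00.

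**4. YQCF acting wholly by lowering severity.** With slopes of 0.5 to 2 and placebo NSAID use of 50%, NSAID use on YQCF comes out at about 33%, and the OR moves from 0.488 to 0.51-0.59.

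**5. Allowing for a baseline severity covariate.** The planned model also contains anti-CCP, RF and DAS28, which would absorb part of U. The null case was repeated by simulation with one baseline marker correlated 0.5-0.7 with U, again an assumption.

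- At 50% vs 30% with slope 1, the bias in the log odds ratio falls from 0.14 to 0.08-0.11. As odds ratios, exp(0.14) = 1.15 falls to exp(0.08) to exp(0.11) = 1.08-1.12.
- At 50% vs 25% with slope 1.5, it falls from 0.29 to 0.18-0.24, that is, from 1.34 to 1.20-1.27.

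The bias shrinks but does not disappear.

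**The case against.** **The trial's efficacy answer does not depend on this model.** This stands in full. The chi-square or Fisher test and Kaplan-Meier contain no NSAID term in either analysis set, and the sample size is built on an unadjusted comparison. A reader might infer from the section heading that the primary analysis is biased or its type I error inflated; the document does not support that.

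**The model is for exploring risk factors.** Its stated purpose is to look at variables that can affect transition, and nothing calls its YQCF coefficient the treatment-effect estimate. This stands as a description and lowers the severity. It does not remove the problem, because the treatment term is in the model, the model is run in ITT, and nothing warns against reading that coefficient as the effect.

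**The timing is inferred.** The word continuous is undefined. A Table 3 footnote sends drugs carried over from before the study into the combined-drugs record, so continuous use could mean NSAIDs already being taken at entry. That is possible. The on-trial reading is more natural, because the only NSAID rule concerns prescribing during the study. If use at entry is meant, the text should say so.

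**The size is assumed.** This stands. The null bias needs YQCF to change NSAID use, and the two-variable model in the table omits the planned covariates, so the upper ends of its ranges are likely too high for the planned model.

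**The treatment term.** A reader might also infer that YQCF use means treatment actually taken. Nothing defines it so, and with ITT specified it is plausible shorthand for the arm.

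**Conclusion.** The point holds for the supporting logistic model only. On the natural reading of sections 2.5, 2.7 and 2.12.1, NSAID use is measured after randomisation. YQCF may change it, since pain is a target of treatment, so the adjusted YQCF odds ratio is not an unbiased estimate of the total randomised effect.

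In the assumed scenarios where YQCF lowers NSAID use, the bias runs against YQCF: an effect of 0.49 is reported as about 0.50-0.68, and no effect as about 1.02-1.46. If NSAID use is the same in both arms, the null odds ratio stays at 1.00. Adjustment for baseline severity reduces the bias. These figures show direction and plausible scale. They are not estimates for this trial.

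Severity is moderate, not must-fix: the covariate is a stated choice and worth correcting, but the main comparison of transition rates stands without it.

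**What to change.** In section 2.12.1, estimate the YQCF effect from a logistic model with the randomised arm and baseline covariates only: sex, age, anti-CCP and RF status, family history, DAS28 at baseline and, if wanted, NSAID use at entry. Table 3 already collects pre-trial medication and drugs carried into the treatment period, so no new data are needed.

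If on-trial NSAID use is of interest as a risk factor, define it and put it in a separate model labelled exploratory. State that the YQCF coefficient in that model is not read as the treatment effect.

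The cost is one extra model and a sentence of text, to be settled before unblinded analysis. Sample size, data collection and clinical management are unchanged.

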#### 2.12.4 Subgroup Analysis

The subgroup analysis of the primary outcome and the secondary outcome will be based on anti-CCP positive or negative.

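### The main test of RA transition leaves out baseline anti-CCP status and is run on both ITT and PP with neither named as primary: a modest loss of power and a small, avoidable ambiguity

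*Protocol article*

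**What the plan says.** - **Main test.** Section 2.12.1 compares the final transition rate by Pearson's chi-square or Fisher's exact test. Neither uses a covariate or stratum. Kaplan-Meier analysis is added to this. A logistic regression then looks for factors that affect transition; its listed variables include anti-CCP but not centre.
- **Analysis sets.** "Per-protocol (PP) analysis and intention-to-treat (ITT) analysis will be applied in chi-square tests, survival analysis, and binary logistic regression". No set is put first. Section 2.12.3, by contrast, names ITT for safety.
- **Anti-CCP.** Section 2.2 defines separate entry routes for positive and negative patients. Table 3 records ACPA at screening. Section 2.12.4 makes subgroups "based on anti-CCP positive or negative". The Discussion says: "Anti-CCP-positive individuals are more likely to develop arthritis and RA as compared to anti-CCP-negative individuals".
- **Randomisation.** Section 2.10 says "a multicenter block random method was used"; section 2.8 plans 30 patients in each of 13 centres. Anti-CCP is not named as a randomisation factor.
- **Sizing.** Section 2.8 uses a two-proportion Z-test. "Power was set at 0.9 and alpha was set at 0.05".

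**The concern.** The trial mixes two groups that the article itself expects to progress at different rates. An unadjusted comparison of proportions counts that difference between groups as noise, although the variable that removes it is already on file for every patient. The Discussion also concedes that the sample size was worked out for anti-CCP-positive patients, so there is little power to spare once negatives are enrolled.

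Separately, if the chi-square gives p<0.05 in one analysis set and not in the other, the article does not say which result decides the trial.

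**Working it through.** **1. The plan's own figure.** Inputs from section 2.8: treated rate 0.5326 ("about 53.26% of patients would transit to RA after 1 year of TCM treatment"), control rate 0.70 ("about 70% of early-stage UA patients with ACPAs meet the 1987 ACR criteria 1-year follow-up"), two-sided alpha 0.05, power 0.90, unpooled variance.

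n = (1.960 + 1.282)² × [0.5326×0.4674 + 0.70×0.30] / (0.70 − 0.5326)² = 172.08, so 173 per group. 346/0.9 = 384.4, so 385. Both stated figures reproduce.

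**2. Power with and without anti-CCP, closed form.** Let f be the share of negatives and q their control-arm rate. Both are assumed. Positives have 0.70 and 0.5326. Negatives are given the same risk ratio, 0.5326/0.70 = 0.761. Evaluable patients per arm: 195 × 0.9 = 175.5.

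- Difference: d = control average − treated average over the mix.
- Unadjusted variance: Vu = pc(1−pc) + pt(1−pt), with the mixed rates.
- Stratified variance: Vs = (1−f)(0.2100 + 0.2489) + f[q(1−q) + 0.761q(1−0.761q)].
- Power ≈ Φ(d/√(V/175.5) − 1.96).

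Worked case, f = 30%, q = 30%:

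- pc = 0.7×0.70 + 0.3×0.30 = 0.580
- pt = 0.7×0.5326 + 0.3×0.2283 = 0.4413
- d = 0.1387, Vu = 0.4902, Vs = 0.4371
- test statistics 2.62 and 2.78

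| Negatives | Their control rate | d | Vu | Vs | Power, unadjusted | Power, stratified |
|---|---|---|---|---|---|---|
| 30% | 30% | 0.1387 | 0.4902 | 0.4371 | 74.7% | 79.4% |
| 50% | 30% | 0.1196 | 0.4857 | 0.4225 | 62.3% | 68.3% |
| 40% | 20% | 0.1196 | 0.4857 | 0.3910 | 62.3% | 71.7% |

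The gains are about 5, 6 and 9 points. The closed form is a large-sample approximation.

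**3. Simulation (13 centres × 30 patients, 1:1 within centre).**

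- Same risk ratio, 10% lost: a gain of about 3 to 4 points at 30%/30%, and about 8 points at 40%/20%.
- Common odds ratio instead, (0.5326/0.4674)/(0.70/0.30) = 0.488, no dropout: 86.9% to 90.8% with 30% negative at 30%; 82.9% to 88.8% with 50% negative at 30%.
- Common odds ratio, 10% dropout: 81.5% to 86.5% with 30% negative at 30%; 77.2% to 82.2% with 50% negative at 30%; 68.1% to 76.6% with 50% negative at 20%.

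Monte Carlo error on each power is 0.4 to 0.9 points.

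**4. Centre.** All patients positive, no dropout, stratifying by centre alone:

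- between-centre SD 0 on the logit scale: 93.2% to 93.0%
- SD 0.3: 91.9% to 92.1%
- SD 0.5: 90.9% to 91.7%
- SD 0.5 with 10% dropout: 85.1% to 86.6%, the largest gain seen

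On top of anti-CCP, centre moved power from 90.0% to 89.4% in one scenario (30% negative at 30%, SD 0.3, no dropout).

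**5. Type I error.** Under no effect, 6,000 trials per scenario, with 10% dropout (no transition counted after leaving) and 0 to 20% further random PP exclusions:

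- chi-square on ITT alone: 4.6 to 4.9%
- chi-square significant in ITT or PP: 6.7 to 7.4%

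**The case against.** The case for the plan is a fair one, and much of it stands.

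- **An unadjusted chi-square is valid.** It keeps its 5% error. Stratifying is a matter of efficiency and does not correct an error. Anti-CCP is also not ignored: it is a logistic covariate and the subgroup factor. This stands, and it is why the point is put as lost power only.
- **The loss depends on figures the article does not give.** This also stands. More extreme inputs (50% negative at 10%) give a gain of about 13 points. But section 2.2 admits negatives only with at least five of seven risk features, and the Discussion calls such patients high-risk, so no weight is put on that case. The low absolute power in the mixed scenarios comes mainly from sizing on positives, which is a separate matter.
- **Ranking ITT and PP is often left to an analysis plan, and running both is a common robustness check.** True. If an analysis plan names the lead set, that half of the point falls away. As published, the article gives both sets to the main test and ranks neither.

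A reader might also infer that no method is designated, so that three methods on two sets make six co-equal chances and an error near 12%. The documents do not support this. The chi-square comes first and matches the two-proportion sizing, survival analysis is introduced as an addition, and the logistic model is there to find factors. No between-group survival test is named, and nowhere may success be claimed on any of the six.

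Nor should a reader infer that omitting centre is costly. Step 4 shows under about 1 to 2 points, and centre as a formal stratum is implied by the wording in section 2.10 and not stated outright.

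**Conclusion.** The point holds in a limited form. The lead method is clear enough. What is missing from it is the one baseline factor the article itself marks as strongly prognostic, and what is unclear is whether ITT or PP decides.

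The cost is about 3 to 6 points of power with 30 to 50% negatives at a 30% control rate, and about 8 points with 40% at 20%. These figures assume the share and rate of negatives, and the same risk ratio or odds ratio in both groups. There is no type I inflation from the omission. The only inflation comes from a free choice between ITT and PP on the chi-square: from 5% to about 7%, under random PP exclusions. This is worth correcting, but it does not threaten the trial's validity.

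**What to change.** State one confirmatory analysis in section 2.12.1 (or confirm it in the analysis plan): a Cochran-Mantel-Haenszel test on the ITT set, stratified by baseline anti-CCP, reported with a stratified risk difference and 95% CI. Centre may be added so that the analysis reflects the multicentre block randomisation, without claiming power for it. Label the PP, survival and logistic results as supportive. In the same edit, say that the anti-CCP subgroups will be assessed by a treatment-by-anti-CCP interaction test.

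The cost is wording only. Anti-CCP is measured at screening and centre is known, so no new data or patients are needed. The change should be dated and made before unblinding.
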